#### Intervention

The initial training plan outlined in Table 1 will serve as a foundation for the development of the final web-based training program. This plan will undergo rigorous revisions in phases 1 and 2 of the research. The finalized web-based training program is delivered as the intervention to participants in this phase 3 of the research. The final program will consist of both mandatory and optional components. This phase will involve a pre-post test administered to participants who have completed at least the mandatory training hours within a two-week timeframe. To promote adherence to the training time duration, participant progress will be closely monitored, and email reminders will be sent every two days. The waitlisted control group drawn from the same pool as the intervention group, helps mitigate selection bias. Control group will be offered the training program after post-test data is collected from both the groups post two weeks.

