#### Sampling design

Sampling involves purposive sampling for recruitment and then random assigned to experimental and waitlist control groups in 1:1 ratio. To ensure allocation concealment, an independent researcher, unaffiliated with this study, will be responsible for generating the randomization sequence. This researcher will not be involved in participant recruitment, enrollment, or data collection. Randomization can be achieved using the research randomizer software [42]. Participants will be blinded to their group assignment throughout the study. Unblinding will only be permitted under exceptional circumstances and with prior approval from the research ethics committee.

The sample size for this study is determined to be 80 participants, considering an anticipated 25% dropout rate. This decision is informed by the considerations outlined in a similar randomized control trial (RCT) to study the efficacy of a skills training program for 58 mental health support providers by Perlman et al. [43]. The sample size of 60 participants will provide 80% power to detect an effect size of 0.8 [44] between the intervention group and the control group at 5% level of significance (two-tailed test) as evidenced in a similar study by Ho et al. [45] with 68 participants.

To explore contrasting perspectives and for an in-depth understanding of the participant’s experiences, focus groups will be chosen using a targeted homogeneity sampling method, aiming to include those with both the highest and lowest score variances on attitude and self-efficacy scales.

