#### Measures

The quantitative data collection for both pre-test (T1) and post-test (T2) time points (before and after completing the online SST training) will utilize the same instruments BAT-Q and COSE-TR. All data will be collected online using google form.

The Beliefs and Attitudes Toward Therapy Questionnaire (BAT-Q) developed by Bolter [28], measures therapists' preferences for long-term versus short-term therapy approaches. Comprising 19 items, the BAT-Q divides into "values" and "attitudes" subscales, resulting in a total score. While the "values" subscale relies on 13 items, the "attitudes" subscale relies on the remaining six. It utilized a seven-point Likert scale and some of the items are reverse scored. A higher subscale and total score suggest higher inclination towards brief therapy. The BAT-Q established itself reliable with Cronbach alpha as 0.88 and acceptable item and test–retest reliability [29, 46]. However, its terminology requires updating for use in the context of SST. The study will adapt BAT-Q to the SST domain by replacing terms like "brief therapy" with "single-session therapy" and "patients" with "clients".

The Turkish version of Counseling Self-Estimate Inventory (COSE-TR) [30] is a shorter version of the original COSE scale [31] with 27 items designed for measuring counseling self-efficacy in collectivists culture. It demonstrates strong internal consistency, with a Cronbach's alpha coefficient of 0.90 and, the four identified factors within the scale display satisfactory reliabilities: Microskills (0.90), Dealing with difficult behaviors (0.71), Cultural competence (0.71), and Counseling process (0.79). The total score represents the overall performance by summing the scores of all individual items across all factors.

To gain a deeper understanding of the factors influencing changes in participants' attitudes, values, and self-efficacy, focus group discussions will be conducted with a purposive sample of participants who exhibit the largest and smallest pre-post test score differences. For participants with large positive score differences, the questions will focus on the specific aspects of the training program that were most helpful. For participants with large negative score differences, the questions will focus on the aspects of the training program that were less effective. The interview schedule will be validated by qualitative research experts.

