#### Procedure

Participants will be recruited using personalized social media messages, targeted social media advertisements, email outreach, flyers within relevant settings, and leveraging the researchers’ professional network. Demographic data as well as their interest in completing in SST training, will be collected through a researcher-developed questionnaire. Participants who show interest in completing the SST training will be randomly allocated to either the intervention group or the control group using the research randomizer software program in 1:1 ratio. The intervention group will have access to the online training program immediately for a period of two weeks. The waitlisted control group will not have access to the online training program during the intervention period, and are offered access after post-test at the end of two weeks.

The pre-test data (T1) is collected using two scales. The first one is a modified version of the BAT-Q Scale [28] with replaced terms like "brief therapy" with "single-session therapy" and "patients" with "clients". These revisions in the item texts of the tool will undergo validation by three psychometric experts. Given that the changes are minor and primarily involve replacing terms to ensure clarity and relevance to the specific context of SST, a consensus among two experts can be considered a reliable validation. The second scale is the counselling self-efficacy scale, COSE-TR [30].

At the end of the two weeks, participants in both the intervention group and the control group will complete a post-test assessment (T2). Participants demonstrating the most significant and least significant changes in attitude and self-efficacy between T1 and T2 will be invited to two separate 30-min focus groups (top 10 and bottom 10, expecting a 50% response rate). This targeted approach facilitates the exploration of contrasting experiences. The SPIRIT Figure in Table 2 explains the schedule of enrolment, interventions, and assessments.

**Table 2 Tab2:** SPIRIT Figure for the Schedule of Enrolment, Interventions, and Assessments

Study period					
	Enrolment	Allocation	Post-allocation		Close-out
Timepoint	T_1_	0	Week 1	Week 2	T_2_
ENROLMENT					
Eligibility screen	X				
Informed consent	X				
Random Allocation		X			
INTERVENTIONS					
SST Training Group			Two weeks access to training		
Waitlist Control Group			No access to training		Two weeks access to training after assessments
ASSESSMENTS					
Quantitative					

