#### Data analysis

Descriptive statistics will be provided for baseline (T1) data. Participant demographics (e.g., age, gender, profession, years of experience, setting) will be described using frequencies and measures of central tendency as appropriate. Internal consistency (e.g., Cronbach's alpha) of both BAT-Q and COSE-TR for Indian population will be evaluated using Jamovi 2.4 software. Missing data will be handled with multiple implementations. Normality of the data will be assessed using the Shapiro–Wilk test.

If the data is found to be normally distributed, independent samples t-test will be used to report the baseline characteristics of the intervention and control groups. ANCOVA will be used to compare the post-intervention outcomes (T2) (self-efficacy, values and attitudes) between the intervention and control groups while statistically controlling for baseline (T1) differences. If the ANCOVA reveals a significant group effect, post-hoc comparisons will be conducted to identify specific differences. Paired samples t-test will be used to analyze changes within each group from pre-test (T1) to post-test (T2) to assess whether there are significant changes over time within each group. If the data is not normally distributed, Templeton’s two-step approach for transformation will be applied. After transformations if the data fails to meet the normality assumption, Mann–Whitney U test will be used to report baseline characteristics. Kruskal–Wallis test can be to identify specific differences between groups. Wilcoxon Signed-Rank Test can be used to assess significant changes over time within each group. All changes will be reported for attitudes, values and four subdomains of self efficacy and p values below 0.05 will be considered significant. Jamovi software will be used for statistical analysis.

To understand the factors influencing the changes observed in the quantitative data, a qualitative analysis will be conducted using six step thematic analysis described Braun and Clarke [38]. Focus group recordings will be transcribed verbatim. The transcripts will be systematically coded, identifying recurring ideas, patterns, and significant quotes related to participants' experiences and explanations for their attitude and self-efficacy changes. Thematic comparisons will be drawn between participants who exhibited significant positive and negative changes in their attitudes, values, and self-efficacy.

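### The protocol contradicts itself on whether intervention participants who do not finish the mandatory training get the post-test; if they do not, the main comparison is open to selection bias

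*Protocol article*

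**What the plan says.** Four parts of Phase 3 of the protocol article bear on who is measured.

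- **Intervention:** "This phase will involve a pre-post test administered to participants who have completed at least the mandatory training hours within a two-week timeframe". The same section has the control group offered the training once post-test data from both groups are in.
- **Measures:** the pre-test (T1) and T2 are placed "before and after completing the online SST training".
- **Procedure:** "Participants who show interest in completing the SST training will be randomly allocated to either the intervention group or the control group", so allocation precedes any training. On controls: "The waitlisted control group will not have access to the online training program during the intervention period". On the post-test: "At the end of the two weeks, participants in both the intervention group and the control group will complete a post-test assessment (T2". Table 2 marks both scales at T1 and T2 and attaches no completion condition.
- **Data analysis:** T2 is compared between groups by ANCOVA adjusting for T1. On missing values: "Missing data will be handled with multiple implementations", which evidently means multiple imputation.

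Sampling design sets 80 participants in a 1:1 ratio, "considering an anticipated 25% dropout rate", leaving 60. The article states no analysis population.

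**The concern.** Completing the mandatory hours happens after randomisation, and only the intervention arm can fail to do it. If T2 goes only to those who finish, the intervention arm is reduced to people who chose to complete the course, while the control arm keeps everyone, including those who would not have finished had they been offered it. The two groups being compared are then no longer the two groups that were randomised.

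The outcomes are self-reported attitudes, values and self-efficacy concerning single-session therapy. People well disposed to the approach may be both likelier to finish and likelier to score high at T2, so the error would tend to favour the training. Adjusting for T1 removes only the part of this that T1 explains.

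The matter cannot wait for an analysis plan. T2 scores not requested at two weeks cannot be recovered. Imputation for non-completers would then have to borrow from completers and controls, with no observed T2 from a single intervention non-completer.

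**Working it through.** **Step 1. Set the passages side by side.**

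| Place | Who has T2 | Completion condition |
|---|---|---|
| Intervention, test sentence | those who completed the mandatory hours | yes |
| Measures | not specified; timed after completing the training | implied |
| Intervention, last sentence | both groups | none stated |
| Procedure | both groups | none stated |
| Table 2 | both scales at T2 | none stated |

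The last three rows do not withdraw the condition in the first, and none says that non-completers are tested. An investigator could follow either instruction and claim to be within protocol.

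**Step 2. Who can fail the condition?** Controls have no access before T2, so a completion rule cannot sensibly be applied to them. In the intervention arm it can exclude anyone who does not finish the mandatory modules, which total 1 + 1 + 4 = 6 hours in Table 1 (a draft that the protocol expects to revise).

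**Step 3. The plan's own figure.** 60 / (1 − 0.25) = 80, so the dropout allowance reproduces: 20 of 80 lost. The plan does not divide that loss between arms or say how much of it is non-completion.

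**Step 4. Size under the restrictive reading.** From the documents: 80 randomised 1:1, so 40 per arm; two-sided 5% test. Assumed, not in the documents: 25% of the intervention arm does not complete, nobody else is lost, the true effect is zero, and completion depends on a normally distributed propensity that has correlation ρ with the T1-adjusted T2 score. This leaves 30 v 40, a loss of 10 of 80, or 12.5% overall. It is not the plan's 25% allowance.

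- Mean shift among completers, in residual SD: ρ × φ(z)/p, with p = 0.75, z = −0.674 and φ(z) = 0.318. The factor is 0.318/0.75 = 0.424.
- Standard error in residual SD: √(1/30 + 1/40) = 0.2415.
- Noncentrality = shift/0.2415; rejection rate from the noncentral t distribution.

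| ρ | Bias (residual SD) | Noncentrality | Rejection of a true null |
|---|---|---|---|
| 0 | 0 | 0 | 5.0% |
| 0.1 | 0.04 | 0.18 | 5.3% |
| 0.2 | 0.08 | 0.35 | 6.4% |
| 0.3 | 0.13 | 0.53 | 8.1% |
| 0.5 | 0.21 | 0.88 | 13.9% |

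**Step 5. Cross-check by simulation.** A null ANCOVA with 4,000 runs, 40 per arm, a T1–T2 correlation of 0.6 (assumed), and the 10 least engaged removed from the intervention arm gave rejection rates of 5.5%, 6.6%, 9.2% and 13.7% at ρ = 0, 0.2, 0.3 and 0.5. The bias on the T2 scale was 0.00, 0.07, 0.10 and 0.16 SD. These are smaller than the table's values mainly because one residual SD is √(1 − 0.6²) = 0.8 of a T2 SD. Applying the same filter to both arms gave estimates within 0.01 of zero, so the harm comes from the filter acting on one arm.

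**Step 6. Sensitivity to the completion rate.** The factor is 0.19 at 10% non-completion and 0.64 at 40%. At ρ = 0.5 the bias is therefore about 0.10 and 0.32 residual SD.

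**The case against.** The strongest reply is that the Intervention sentence cannot be meant literally. A pre-test cannot be restricted to people who have already finished the course, and the literal wording would also shut controls out of a post-test that the same section gives them. The sentence stands among remarks on mandatory content and reminders, so it may only describe the expected training dose. The parts that set the schedule, Procedure and Table 2, test both groups without condition, and a missing-data method suggests that incomplete cases are kept. On that reading the comparison stays randomised.

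Much of this stands. A reader might infer that the trial has settled on testing completers only and has already given up its randomised comparison. The documents do not support that: the restrictive reading is one of two, and the word *only* is not in the sentence.

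It is also fair that the correlations have no source in the protocol. Participants must commit to the two weeks and express interest before allocation, which may narrow differences in motivation. Even the upper end of the illustrated bias is small against the planned effect size of 0.8. And if losses were equal in the two arms and similarly related to outcome, the bias would largely cancel.

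The contradiction remains. The timing given under Measures leans the same way as the Intervention sentence, no text says that non-completers are tested, and the missing-data sentence does not say that they are retained.

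**Conclusion.** The point holds as an internal contradiction about who is measured at T2, and it should be resolved before data collection. That a completion rule would act on one arm only, and after randomisation, follows from the waitlist design and needs no assumption.

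The size of the harm is conditional. It arises only if the Intervention sentence is applied as a filter, and only if completion is related to the T1-adjusted outcome. With 25% non-completion confined to the intervention arm and ρ from 0 to 0.5, the bias is 0 to 0.21 residual SD and the type I error about 5% to 14%. The documents supply neither the completion rate nor the correlation, so this is an illustration and not an estimate for this trial.

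**What to change.** Replace the test sentence under Intervention with wording such as:

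> *T2 is requested at two weeks from every randomised participant in both arms, whatever training hours were completed. The primary ANCOVA compares arms as randomised, with multiple imputation for missing T2.*

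Bring the timing phrase under Measures into line, so that T2 is defined by the two-week point and not by completing the training. Report those who completed the mandatory hours only as a supplementary adherence analysis. Procedure and Table 2 already fit this wording.

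The cost is sending the existing online form to intervention participants who did not finish, and possibly a slightly less favourable estimate. Training content and sample size are unchanged.

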#### Participants

Mental health support providers (e.g., psychologists, counsellors, social workers) from India, who express interest in completing the SST training program will be invited to participate. Eligibility criteria will require participant to be either in their final year or have completed a Master's program in psychology or social work from India. They should commit availability to participate in the 2 week long study. Participants who have received SST training in the past are excluded. Those currently in any treatment for mental illness will also be excluded. Age and gender will not be not a criterion for exclusion. The quantitative component of this phase will require a large sample size. Potential recruitment strategies include reaching out to universities offering mental health related master's level programs, training institutes offering CPD trainings, collaborating with country-specific mental health societies and organizations, utilizing social media platforms or online forums, targeted email invitations and employing snowball sampling techniques. Offering incentives like certificates of completion can motivate potential participants.

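### T2 follow-up is not kept separate from training reminders, so reasons for returning T2 can differ by arm and less engaged trainees may be lost selectively

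*Protocol article*

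**What the plan says.** All of this is in Phase 3 of the protocol article.

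- **Contact between T1 and T2 (Intervention):** "To promote adherence to the training time duration, participant progress will be closely monitored, and email reminders will be sent every two days". The arm is not named. No other contact between the two assessments is stated.
- **Access (Procedure):** "The intervention group will have access to the online training program immediately for a period of two weeks". For the other arm: "The waitlisted control group will not have access to the online training program during the intervention period, and are offered access after post-test". Table 2 shows the same.
- **Timing of the offer to controls (Intervention):** "Control group will be offered the training program after post-test data is collected from both the groups post two weeks".
- **Who is tested:** Intervention says "This phase will involve a pre-post test administered to participants who have completed at least the mandatory training hours within a two-week timeframe". Procedure says of the end of the two weeks that "participants in both the intervention group and the control group will complete a post-test assessment (T2".
- **Incentive (Participants, among the recruitment strategies):** "Offering incentives like certificates of completion can motivate potential participants". It is tied neither to an arm nor to T2.
- **Expected loss (Sampling design):** "The sample size for this study is determined to be 80 participants, considering an anticipated 25% dropout rate". The figure is not split by arm.

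**The concern.** The outcomes are self-completed online forms with one post-test, so the comparison depends on who returns T2. In the plan as described, the effort made between visits goes into getting trainees through the modules. Nothing stated pursues the T2 form itself in either arm.

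A trainee who has fallen behind may also be one whose attitudes and self-efficacy moved little. If such trainees tend not to return T2, or are not offered it because they did not finish the mandatory hours, the trainees left for analysis are the more engaged ones. Controls cannot be lost by that route, because before T2 they have no training to fall behind on.

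The planned ANCOVA adjusts for T1. Engagement with the modules arises after randomisation and T1 need not predict it, so loss tied to engagement can leave a bias that the adjustment does not remove.

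**Working it through.** **1. Whom the contact can reach.** Reminders every two days over 14 days come to about 14 / 2 = 7 per trainee. Controls have no access in weeks 1 and 2, so they have no progress to monitor and no training to be reminded of. The contact is one-sided by implication, although the text does not say so.

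**2. What is still to come at T2.** Trainees' two-week access has run. Controls, who enrolled because they were interested in the training, have yet to receive it. The offer follows collection of T2 from both groups, and it is not stated to depend on a control's own form.

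**3. Who is given the tests.** Under Intervention, testing is tied to finishing the mandatory hours. Before T2 that condition can act as a filter only among trainees. Under Procedure, both arms complete T2 with no such condition. The two statements need to be reconciled.

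**4. The plan's own figures.** 60 / (1 − 0.25) = 80, so the dropout step reproduces. That is 20 lost of 80, with 40 randomised per arm. For an effect of 0.8 at two-sided 5%, a t test with 30 per arm has 86.1% power, and 26 per arm would give 80%. The stated 80% is therefore conservative. If the 60 returners split 24 and 36 instead of 30 and 30, power is still 84.7%. The issue is bias, not power.

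**5. Illustration of bias.** Let p be the fraction of an arm lost, and d the gap in mean change (in SD) between those who stay and those who are lost. The mean of the whole arm is the mean of the stayers minus p × d, so

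bias = (p × d in trainees) − (p × d in controls).

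Assumptions: d = 0.5 among trainees; overall loss 25% as planned; the split by arm is invented. The last column takes d = 0.5 among controls too.

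| Trainee loss | Control loss | Bias if control loss is unrelated to outcome | Bias if control loss is equally selective |
|---|---|---|---|
| 25% | 25% | 0.25 × 0.5 = 0.125 | 0.125 − 0.125 = 0 |
| 35% | 15% | 0.35 × 0.5 = 0.175 | 0.175 − 0.075 = 0.10 |
| 40% | 10% | 0.40 × 0.5 = 0.20 | 0.20 − 0.05 = 0.15 |
| 15% | 35% | 0.15 × 0.5 = 0.075 | 0.075 − 0.175 = −0.10 |

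Halving d halves every entry. The first row matters most: with equal return rates there may still be a bias if only one arm's loss is related to outcome, and none if both arms' loss is related to it equally.

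**6. A second model.** There is no true effect, return depends on a latent variable correlated 0.3 or 0.5 (assumed) with the outcome, and completers are compared without adjustment. With 75% return in both arms and selection among trainees only, the bias is 0.13 to 0.21 SD and the two-sided error is 8% to 13% instead of 5%. With the same selection in both arms and 65% of trainees against 85% of controls returning, it is 0.09 to 0.15 SD. With those rates swapped it is −0.09 to −0.15 SD.

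**The case against.** The strongest reply is that nothing in the quoted sentence is wrong. The reminders belong to the delivery of the training, and a waitlist arm has nothing to be reminded about. Some difference in contact, and training still to come for controls, go with any waitlist design. A condensed article may also leave the T2 mailing schedule to the full protocol, and Procedure is even-handed about T2. This stands in part: the difference in contact is not an error in itself, and the lack of a published mailing schedule is no finding. What remains is that Intervention, as written, links testing to finishing the modules and pursues trainees only for that purpose.

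Three stronger readings are tempting, and the documents support none of them.

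- *T2 return is likely to be lower among trainees.* No rate by arm is given. Reminders may keep trainees engaged and pending access may keep controls engaged, so the two could offset each other.
- *The effect is inflated by some 16% to 25% of the planned 0.8.* That range is 0.125 / 0.8 to 0.20 / 0.8. It appears only if trainee loss is selective and control loss is not. The last column of the table shows it shrinking, vanishing or changing sign.
- *Controls must return T2 to obtain the training, while certificates reward trainees alone.* Access is not stated to depend on a participant's own form, and the certificate is not assigned to an arm.

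The Data analysis section also names a missing-data method, apparently multiple imputation. It may help, but in its usual form it does not repair loss that depends on an unobserved outcome.

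**Conclusion.** The concern holds as a risk of bias that is cheap to reduce. The stated contact before T2 can reach only trainees and serves training completion, and the article gives two different accounts of who is tested. Reasons for returning T2 can therefore differ by arm, and less engaged trainees may be lost selectively.

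Direction and size are unknown. The 0.125 SD figure is an illustration resting on three assumptions: 25% loss among trainees, a gap of 0.5 SD between those lost and those who stay, and control loss unrelated to outcome. The first borrows the plan's overall dropout figure; the other two have no source in the documents.

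**What to change.** Separate training reminders from T2 follow-up, and state in the Intervention and Procedure sections, in the same terms, that:

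- everyone randomised, in both arms, receives the same T2 invitation and the same T2 reminder schedule, starting on the same fixed day after allocation;
- this applies regardless of how many modules have been completed, so that the completion condition under Intervention no longer decides who is tested;
- training reminders continue as planned but are separate messages from the T2 follow-up;
- certificates are issued only after the T2 window has closed;
- T2 return is reported by arm.

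Extra messages to controls at the trainees' two-day frequency are not needed for this, and could themselves alter engagement in the control arm.

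The cost is some automated emails and a later certificate date, with no new staff or visits. The downside is that trainees wait a short time for certificates. The change should be made before Phase 3 recruitment, because selective loss cannot be reliably repaired in the analysis.
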